### Sample size

For the power analysis we made some simplifying assumptions: only pre- and post-intervention periods are compared and instead of comparing slopes we compare levels of infection rate. Under these circumstances a length of 1.9 years before and after intervention (leading to an assumed number of 141 cases before) is enough to detect a drop in rate to 70%. When we apply loglinear regression analysis with Poisson error distribution corrected for number of days at risk we find that that two times 1.9 years leads to a power of 80%.

The baseline rates of adherence to the insertion and maintenance bundles are estimated at 60% and 20%, respectively; the post intervention rates aimed at are 100% and 45%, respectively. Sample size calculation indicated that each sequential period requires 15 insertion observations and 45 maintenance observations to detect a relative difference of 37% and 125% alpha of 0.05 and a 1-beta of 0.8.

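### The adherence figures do not follow from one calculation: 37% is not the 60% to 100% difference, and 45 maintenance observations give about 72% power under the two-sided convention that yields 15 for insertion

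*Protocol article*

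**What the plan says.** The second paragraph of the Sample size section in the protocol article covers the two adherence outcomes. The rates are "estimated at 60% and 20%, respectively; the post intervention rates aimed at are 100% and 45%, respectively", insertion first and maintenance second. It then states that "each sequential period requires 15 insertion observations and 45 maintenance observations to detect a relative difference of 37% and 125" per cent, with "alpha of 0.05 and a 1-beta of 0.8". It gives no test and does not say whether alpha is one-sided or two-sided. These are the only sizing figures for adherence to the insertion and maintenance bundles, which are objectives 2 and 3 and the secondary outcomes.

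**The concern.** The paragraph gives every input needed to check it, and two of its figures do not fit the rest.

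- The relative difference for maintenance, 125%, is the rise from 20% to 45% expressed relative to baseline. On that same scale the rise from 60% to 100% cannot be 37%.
- The insertion number of 15 is what the usual two-sided formula gives. The maintenance number of 45 is below what that formula gives for 20% versus 45%.

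At stake is the stated power for maintenance adherence, and a reader's ability to tell which insertion effect the plan is sized for. If 45 is the number compared between periods and the test is two-sided, the chance of missing the targeted improvement is about 28% rather than 20%.

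**Working it through.** **Inputs**, all from the Sample size section: insertion 60% to 100%, 15 per period; maintenance 20% to 45%, 45 per period; alpha 0.05; power 0.80. Equal numbers in the two periods are assumed, as the wording implies, and observations are treated as independent.

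**Relative differences**

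- Maintenance: (45 − 20)/20 = 125%. This matches the article and fixes the scale as relative to baseline.
- Insertion: (100 − 60)/60 = 66.7%, or 40 percentage points in absolute terms. Neither is 37.

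**Formula** (two proportions, normal approximation, pooled variance under the null, with p̄ the mean of the two rates):

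n per period = [z_α √(2p̄(1 − p̄)) + z_β √(p₁(1 − p₁) + p₂(1 − p₂))]² / (p₂ − p₁)²

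Power at a given n = Φ{[(p₂ − p₁)√n − z_α √(2p̄(1 − p̄))] / √(p₁(1 − p₁) + p₂(1 − p₂))}

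Here z_α = 1.960 two-sided or 1.645 one-sided, and z_β = 0.842.

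**Insertion, two-sided** (p̄ = 0.80)

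- n = (1.109 + 0.412)² / 0.16 = 14.5, so 15. The article's number is reproduced.
- Power at 15: (0.40 × √15 − 1.109)/0.490 = 0.899, so 81.6%.

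**Maintenance, two-sided** (p̄ = 0.325)

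- n = (1.298 + 0.537)² / 0.0625 = 53.9, so 54. The article's 45 is not reproduced.
- Power at 45: (0.25 × √45 − 1.298)/0.638 = 0.593, so 72.4%.

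**Same formula, one-sided**

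- Maintenance: (1.090 + 0.537)² / 0.0625 = 42.3, so 43. Power at 45 is 82.1%.
- Insertion: (0.930 + 0.412)² / 0.16 = 11.3, so 12.

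| Convention (pooled formula) | Insertion, 60% v 100% | Maintenance, 20% v 45% |
|---|---|---|
| Article | 15 | 45 |
| Two-sided 0.05 | 15 | 54 |
| One-sided 0.05 | 12 | 43 |

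**Does the choice of two-sided method matter for maintenance?**

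| Method, two-sided 0.05 | Power at 45 per period | Needed for 80% |
|---|---|---|
| Pooled normal | 72.4% | 54 |
| Unpooled normal | 74.8% | 52 |
| Arcsine | 73.1% | 54 |
| Continuity-corrected | 64.1% | 62 |
| Chi-square, exact enumeration | 73.9% | – |
| Fisher, exact enumeration | 65.9% | – |

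None reaches 80% at 45. With Fisher's exact test, 54 per period gives only 74.7%, so the test has to be named along with the sidedness. For insertion at 15 per period, Fisher gives 78.3% two-sided, close to the stated 80%.

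**The case against.** **Sidedness is not stated, and the hypothesis is directional.** The article's hypothesis is that implementation promotes adherence, so a one-sided test is conceivable, and with it 45 maintenance observations are enough on the pooled formula. This stands, and it is why the 72% must be conditional. It does not rescue the paragraph, because the one-sided formula gives 12 for insertion. Rounding 12 and 43 up to the next multiple of five would return 15 and 45, but the article mentions neither a one-sided test nor such rounding. One-sided testing of 60% versus 97% (37 absolute points) would give 15 and 43, but that contradicts the stated 100% target. In each case 37% is still not the relative difference for the stated rates.

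**A reader might infer that both adherence sample sizes fail.** They do not: 15 insertion observations deliver about 80% power for 60% versus 100%.

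**A reader might also take 37% literally**, as a rise from 60% to 82%, for which 15 observations would be far too few. The article never sets 82% as a target. It states 100%, and 15 reproduces from 100%, so 37% is best read as a wrong label rather than a second, undetectable target.

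**The period is not defined.** The Study design section speaks of three-month periods within three phases, and outcomes are measured quarterly. If 45 is a quarterly number and quarters are pooled, the shortfall disappears: two quarters on each side, 90 versus 90, would give 95% two-sided power for independent observations. If the period is a whole phase, or if single quarters are compared, the shortfall remains. The required numbers also read as minima rather than caps.

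**These are secondary process outcomes.** The power calculation for the infection rate is separate and is not touched by this point.

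**Conclusion.** The adherence paragraph is wrong as written, in a narrow sense. The 37% is incorrect for the stated insertion rates whatever test is used; the figure is 67% relative, or 40 percentage points. The insertion number of 15 is sound for 60% versus 100% at two-sided 0.05 (81.6%). Under that same convention the maintenance number of 45 gives about 72% power for 20% versus 45%, and 80% needs 54, a gap of 9 observations per period. Of the conventions tried, none returns both 15 and 45 directly from the stated rates.

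The 72% rests on two-sided testing, independent observations and a comparison of 45 with 45. The article does not settle the first or the last of these, so it does not support a flat statement that maintenance adherence is under-powered. It does support the statement that the rates, the 37% and the two sample sizes need to be reconciled.

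**What to change.** In the Sample size section:

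1. Replace 37% with 67% (40 percentage points).
2. Name the test and say whether alpha is one-sided or two-sided.
3. If two-sided, restate the power of 45 maintenance observations per period as about 72% for 20% versus 45% (normal approximation), or, optionally, set the target at 54. If Fisher's exact test or a continuity correction is intended, recompute the number, since 54 is then not enough (62 with the continuity correction).
4. If one-sided, say so and reconcile the insertion number, which would be 12 rather than 15.

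The cost is one corrected sentence. The optional increase is 9 more maintenance observations per period, made by the nurse observers already planned. No patient numbers change.

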### Secondary outcomes

Rate of adherence to the CVC insertion bundle and rate of adherence to the maintenance bundle will serve as secondary outcomes.

The attending nurse will assess adherence to the CVC insertion bundle during the insertion procedure (Table 3). To this aim we designed a digital tab with drop-down menu for the two different patient data management systems. The time out procedure prior to the CVC insertion is predominantly added for creating safety awareness during insertion (Additional file 1: Table S1). During the insertion procedure all involved healthcare workers are encouraged to make comments and to stop the procedure in case of violation of insertion bundle. Intravenous medication preparation and administration items will serve to measure adherence to the CVC maintenance bundle (Table 4). Purpose-trained nurses will randomly assess these items during planned daily care.

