### Data collection

Four nurses trained in observation will unobtrusively observe staff when they apply the insertion and maintenance bundles. Observation will be guided by a self-designed structured case report form. The staff will be unaware of the reason for the observations; they are already frequently observed for training or research purposes. Data collection will be at random moments seven days a week and 24 hours a day. Sealed envelopes will be used to ensure an equal allocation of these two-hour observations over the wards and observation times during the day. Data on sex, (birth) weight, and age of the patients involved will be retrieved from the patient data management systems (Additional file 3: Table S2). Disease severity of infants admitted to the neonatal intensive care unit will be documented by the Clinical risk index for babies (CRIB) score [32]; that of children admitted to the pediatric intensive care unit by the Pediatric Risk of Mortality III score (PRISM III) [33] or Pediatric Index of Mortality (PIM) score [34]; that of children admitted to the oncology department by the Lansky score (children ≤ 9 year) [35] or Karnofsky score (children > 10 year) [35]. There is no suitable disease severity score for patients admitted to the medium care ward, due to the diversity of diseases.

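### The 45 maintenance observations per period give about 72% power, not 80%, under a two-sided test of independent observations, and less if several acts per two-hour block are counted

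*Protocol article*

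**What the plan says.** The Sample size section gives the planning rates for adherence: "The baseline rates of adherence to the insertion and maintenance bundles are estimated at 60% and 20%, respectively", and "the post intervention rates aimed at are 100% and 45%, respectively". It concludes that "each sequential period requires 15 insertion observations and 45 maintenance observations". The stated basis for both numbers is an alpha of 0.05 and a power of 0.8, with relative differences of 37% for insertion and 125% for maintenance. It names no sidedness, design effect, intraclass correlation or number of sessions.

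The Data collection section describes how the observations arise. "Four nurses trained in observation will unobtrusively observe staff when they apply the insertion and maintenance bundles", and "Sealed envelopes will be used to ensure an equal allocation of these two-hour observations over the wards and observation times during the day". The Secondary outcomes section says what is scored for maintenance, namely the intravenous medication preparation and administration items of Table 4: "Purpose-trained nurses will randomly assess these items during planned daily care".

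The Statistical analysis section gives methods for the infection rate and for cost-effectiveness. It states no test for adherence.

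**The concern.** Two features of the maintenance sample size look wrong.

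- **The number itself.** Forty-five per period looks small for 20% against 45% at the usual two-sided 5% level, even if every observation is independent.
- **The sampling scheme.** Observers work in two-hour blocks on a ward. Such a block could contain several preparations or administrations, possibly by the same staff under the same conditions. Acts within a block would then tend to be alike, and 45 acts would carry less information than 45 independent ones. The calculation has no term for this.

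Adherence is a secondary outcome, the subject of two of the four objectives and one half of the stated hypothesis. It is also reported back to the wards each quarter to steer the programme. If power is overstated, a real improvement may be missed. If correlated acts were analysed as independent, chance changes would be reported as real too often.

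**Working it through.** **Inputs from the article (Sample size).** p1 = 0.20, p2 = 0.45, alpha = 0.05, power = 0.80, equal numbers per period. The stated relative difference of 125% agrees: 0.45/0.20 − 1 = 1.25.

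**Inputs not in the article, assumed here.** Acts per block m = 3; intraclass correlation (ICC) 0.05 to 0.3.

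**Step 1: reproduce the 45 with independent observations.** Pooled two-proportion formula without continuity correction:

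n = [z_a·√(2·p̄(1−p̄)) + z_b·√(p1(1−p1) + p2(1−p2))]² / (p2−p1)²

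Here p̄ = 0.325, so the first root is √0.43875 = 0.6624. The second is √(0.16 + 0.2475) = 0.6384, and z_b = 0.8416.

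- Two-sided, z_a = 1.960: (1.2982 + 0.5373)² / 0.0625 = 53.9, so 54.
- One-sided, z_a = 1.645: (1.0895 + 0.5373)² / 0.0625 = 42.3, so 43.

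Other variants: 62 (two-sided with continuity correction), 51 (one-sided with correction), 52 (two-sided unpooled), 54 (two-sided arcsine). Only the one-sided uncorrected formula comes near 45.

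**Step 2: power with 45.** Power = Φ{[0.25·√n − z_a·0.6624] / 0.6384}, with 0.25·√45 = 1.6771.

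- Two-sided: Φ(0.593) = 72.4%. Fisher's exact test gives 65.9%.
- One-sided: Φ(0.920) = 82.1%.

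**Step 3: which sidedness was used?** The companion figure is 15 insertion observations for 60% to 100%. The same pooled formula gives 14.5, so 15, two-sided, and 11.3, so 12, one-sided. The one-sided formula with continuity correction gives 16 for insertion, but 51 for maintenance. No single variant tried gives both 15 and 45. The evidence from the 15 is limited, because the 37% stated beside it does not match 60% to 100% (1.00/0.60 − 1 = 67%).

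**Step 4: effect of blocks, if several acts per block are counted.** Design effect DE = 1 + (m − 1)·ICC and effective n = 45/DE, entered in the power formula of step 2. The needed number is 54·DE, rounded up. The type I error of a two-sided test that ignores the blocks is 2·[1 − Φ(1.96/√DE)].

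| m = 3, ICC | DE | effective n | power, two-sided | power, one-sided | needed, two-sided | type I error if blocks ignored |
|---|---|---|---|---|---|---|
| 0.05 | 1.1 | 40.9 | 68.1% | 78.8% | 60 | 6.2% |
| 0.1 | 1.2 | 37.5 | 64.2% | 75.5% | 65 | 7.4% |
| 0.2 | 1.4 | 32.1 | 57.4% | 69.6% | 76 | 9.8% |
| 0.3 | 1.6 | 28.1 | 51.7% | 64.4% | 87 | 12.1% |

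With m = 1, DE = 1 at any ICC, and step 2 stands unchanged.

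**Step 5: simulation check of the type I error.** With 9 sessions of 5 acts per period, ICC 0.10 (DE 1.4), new sessions in each period and no true change, a simple two-sided comparison rejects in 10.3% of runs; the formula gives 9.8%. With the same clusters in equal numbers in both periods, as with wards under equal allocation, it rejects in 4.3%.

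**The case against.** **The test may be one-sided.** Sidedness is not stated and the hypothesis is directional. On that reading 45 gives 82% and the claim is met, before any clustering. This stands as a possibility. It leaves the 15 for insertion unexplained, since the same one-sided formula gives 12.

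**An observation may be a block.** The Data collection section applies the word to the two-hour blocks, and the Sample size section counts observations. If each of the 45 is a separate block, clustering by session disappears. The article does not settle this, so the objection makes the clustering part conditional. It does not touch the 72%.

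**Forty-five may not be the total per phase.** The Study design section has several three-month periods within three phases. If 45 were collected each quarter, two quarters would give 90, which covers 54 up to a design effect of 90/54 = 1.67. That is a fair point about a pooled comparison of phases. The sentence itself, however, claims 80% power for the number in each period.

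**No adherence test is stated.** An article may leave that to a fuller plan. The type I figures therefore describe what would follow from ignoring the blocks, and are not a fault in a stated analysis.

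**Stronger readings.** A reader might infer that clustering certainly removes the 80% power. The documents do not support this, because they give neither the ICC nor the acts per block. A reader might also infer that correlation within wards makes intervals too narrow. Observations are allocated equally over wards, so with the same wards in both periods the ward effect largely cancels in the before-after difference, as step 5 shows.

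**Conclusion.** The point holds in two parts of different strength.

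- **Firm, given a two-sided 5% test and independent observations:** 45 per period gives about 72% power, and 54 are needed for 80%. The stated 80% is reached only one-sided, and the article does not say which test it used.
- **Conditional on several acts per block being counted:** the calculation has no allowance for the blocks. At an assumed 3 acts per block and ICC 0.05 to 0.3, power is 68% to 52% two-sided and 79% to 64% one-sided, so even the favourable reading falls below 80%. A two-sided comparison that ignored the blocks would have a type I error of about 6% to 12%. If each observation is its own block, none of this arises.

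The matter deserves correction because a published power figure depends on an unstated choice of test and an undefined unit. It concerns a secondary outcome and does not affect the sample size for the infection rate.

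**What to change.** 1. State whether the test is one-sided or two-sided.
2. Restate the power of 45 observations: about 72% two-sided under independence, and lower over a stated range of design effects if acts within blocks are counted.
3. Define the observation. Either count one observation per two-hour session as the unit, or record a session identifier and analyse adherence with session as the cluster (GEE or a random-intercept logistic model) and ward as a factor.

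The cost is small. The envelope scheme already creates the sessions, so the identifier is one extra field on the observation form. The price is wider intervals and a lower stated power. Keeping 80% two-sided would instead mean at least 54 observations per period, multiplied by the design effect where acts within blocks are counted.

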### Ethical aspects

The Erasmus MC Institutional Review Board approved this study (MEC-2012-375).

## Discussion

The implementation strategy encompasses a multifaceted program tailor made for this specific hospital and ready for use. We hypothesize that implementation of this program will result in fewer CA-BSIs and improved adherence to CVC bundles [5,22,24,37]. Tailored implementation strategies – i.e. based on content analysis of barriers and facilitators – seem to be more effective than non-tailored strategies [38,39]. The Pronovost-model effectively helped to design strategies from the first to the last phase.

Various strategies will be employed. First, education by means of a mini-symposium, workshops, presentations, and so on. Second, improving staff intrinsic motivation, e.g. by audit, feedback, and reminders. Third, organisational change: preparing on single protocol for all patients. Fourth, use of ICT: e.g. a timer on the computer screen at the bedside to clock the 30 seconds air drying time, online access to guidelines and the CVC infection prevention manual, use of screen savers, and daily reminder informing whether the CVC is still needed. Fifth, feedback: quarterly reporting of the CA-BSI incidence and the rates of adherence to the insertion and maintenance bundles. Sixth, awareness: time out procedure and daily goal sheet. Seventh, engagement of the managing staff: showing their commitment to the aim.

The Pronovost-model recommends enlisting all local stakeholders involved in patient care and discussing with them potential barriers and facilitators to adherence to the developed protocol. The Pronovost-model does not provide for eliciting support from senior management of the hospital. Nevertheless, they will be asked to demonstrate their commitment and assume ownership of the general aim to reduce CA-BSIs hospital-wide [25]. We will explicitly designate senior management as ambassadors of the goals [40] by publishing their one-liners and portrait pictures. These ambassadors should convince all healthcare workers that safer CVC care is an important goal and make clear they support the campaign. The senior management is officially accountable for patient safety and even may act as role models.

Use of opinion leaders will be added to the implementation strategy. Clinical and senior management need to show their vision and clearly dissimilate this particular aspect of safety culture. Senior management of effective infection prevention programs dissimilated their success as improved clinical excellence and inspired their staff [26]. Furthermore, senior management will help resolve organizational and financial barriers and practically support initiatives [25,26].

The Pronovost-model describes the implementation process in broad terms; development of a fitting protocol or work-instruction is not included [12]. We will therefore add a comprehensive description of how to develop a work-instruction. Evidence from recently published studies should support the newly developed protocol and providing evidence will perfectly fit into phase 1 of the Pronovost-model; building evidence in favour for the chosen intervention.

Feedback is a widely used, powerful measure to increase adherence to infection prevention measures such as good hand hygiene [24,41]. However, once feedback is stopped any unwanted behaviour could come up again [24,42]. On the other hand, providing continuous feedback is time consuming and therefore not realistic. Feedback should be used firstly to alter initial unwanted behaviour and this should ideally move into desired behaviour as an intrinsic driven and well-conditioned behaviour.

Education is often used to support behavioural change, especially if flaws in knowledge are observed [5,40,43]. A complicating factor is that level of knowledge varies among healthcare workers categories and within categories. This should be borne in mind when developing a hospital-wide education program. Physicians may tend to appreciate knowledge more than do nurses, and evidence-based education could be very useful to promote physicians’ desired behaviour [44]. On the other hand, a wash-out effect is often observed [45,46]. This means that knowledge previously received may recede to the background. Ideas on what is effective in infection prevention are developing over time, so regular updates are essential. In addition, repetition of education programs is necessary in a teaching hospital like ours; many healthcare workers are in training and leave the hospital after having completed their education program.

The Pronovost-model is merely medical oriented. The main point of departure from the model is knowledge transfer, which fits into physicians’ learning style [44]. Goossens et al. found that strong scientific evidence was the strongest determinant of physicians’ behaviour [44]. However, regarding our goal, a clear healthcare team angle seems to be more appropriate for a broad dissimilation of improved hygienic behaviour among all members of the multidisciplinary team. Nurses have a more active learning style, and the strongest determinant of knowledge acquisition was found the be the fact whether the subject was 'interesting […] or not’ [44]. This phenomenon affects whether a new procedure is potentially beneficial for patients or gets embedded in the daily care.

We postulate that the proposed study has methodological strength because it is guided by a validated implementation model that has been translated into a hands-on program and is described in detail for implementation hospital-wide. Furthermore, regularly reporting the outcomes is in line with the ORION statement promoting transparent reporting on intervention studies aimed to reduce nosocomial infections. ORION recommended interrupted time series as preferable method for analysis showing the change in results over time.

We anticipate several challenges in this study. (1) Effectiveness of interventions is preferably evaluated by randomisation into an intervention and control group. However, this method is inappropriate for our aim to implement an intervention hospital-wide, and the interrupted time series design is the second best solution and in line with the ORION guidelines (2). The CVC bundle is adapted and tailor made for our hospital. Although this results in less generalizability, this naturalistic approach could help develop practical implementation strategies for other hospitals or other interventions. (3) The effective ingredients of the bundle are still unclear. However, as some interventions have been shown to be effective it would be unethical to test all separate interventions. (4) To control for confounders is a challenge due to the different safety climates in the different departments. By establishing a clear leadership we will try to show the benefits of a univocal approach towards infants’ CVC care.

Nevertheless, this detailed implementation strategy of the CVC bundle has a potential to effectively modify healthcare workers behaviour and reduce the number of CA-BSIs hospital-wide.

